### Patient Selection

Inclusion and exclusion criteria are shown in Table 1. In summary, the study will include patients undergoing extracorporeal VAD implantation surgery to treat refractory congestive heart failure that needs mechanical circulatory with or without pulmonary support.

**Table 1 Tab1:** Study inclusion and exclusion criteria

Inclusion criteria	
Patients may enter the trial if all of the following apply:	
1. Age 12 years or older and younger than 80 when providing consent.	
2. To receive an extracorporeal ventricular assist device to treat acute cardiogenic circulatory failure.	
3. Written informed consent from the patient or legal representative/close relative	
Exclusion criteria	
Patients may not enter the trial if any of the following apply:	
1. History of cardiac or great vessel surgery	
2. Participating in another clinical trial at time of enrolment	
3. Deemed unsuitable by the primary investigator for other reasons	

### Group Allocation

Eligible patients will be registered and randomly assigned in a 1:1 ratio to either the surgery with BAX602 group (group A) or the surgery-alone group (group B), using permutation block randomization stratified by site. To ensure concealment, the block sizes will not be disclosed. Owing to the nature of the intervention, the investigators cannot be blinded to the allocations. Assessments regarding adhesion severity will be conducted by the operator of the re-thoracotomy in the presence of the cardiothoracic surgeon who is not involved in the primary thoracotomy. Video footage of the surgical field will be collected during re-thoracotomy.

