Several adhesion prevention reagents have been proposed. The application of Coseal spray (Baxter Healthcare Corporations, Deerfield IL, USA), hereafter referred to as BAX602, over the epicardium and the great vessels reportedly contributes to adhesion prevention after surgical procedures, including cardiac surgery [10, 11] and even VAD implantation surgery [12, 13]. BAX602 is composed of two synthetic polyethylene glycols (PEGs): a dilute hydrogen chloride solution and a sodium phosphate/sodium carbonate solution. When these two solutions mix, they polymerize to form a hydrogel that inhibits adhesion formation. Spraying the heart and the great vessels with BAX602 causes this hydrogel to coat the surface of the heart and the great vessels; this hydrogel coating is sustained for 7 days before being hydrolyzed, consequently preventing adhesion formation over the surface of the heart and the great vessels [11]. Although there are positive reports of the use of BAX602 in pediatric cardiac surgery in observational [11] and prospective randomized [10] studies, the safety and efficacy of BAX602 for adhesion prevention have not been fully established in adult patients with an implanted VAD.

Because no devices have been approved in Japan for tissue adhesion prevention of thoracic organs, including cardiac surgical cases, this investigator-initiated trial of BAX602 was designed as a multicenter phase I/II randomized controlled study. The aim of this proposed study is to evaluate the safety and effectiveness of spraying BAX602 over the surface of the heart and great vessels for adhesion prevention in patients undergoing extracorporeal VAD implantation surgery to treat refractory congestive heart failure. The subsequent goal of this study is the approval of BAX602 for adhesion prevention in cardiac surgery in Japan.

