### Study Setting

The study is an investigator-initiated, multicenter, pivotal, two-arm, open-label, randomized trial. The flowchart of the trial is shown in Fig. 1.

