### Assessment of Adhesion

Pericardial adhesion will be macroscopically evaluated during VAD explant surgery performed 2–12 weeks after the primary surgery. The VAD explant surgery is performed to either wean the patient from the VAD as a result of sufficient cardiac functional recovery or to exchange the initial VAD with a durable VAD as a result of insufficient recovery [14]. Patients who undergo VAD explant surgery 1–13 days after the primary thoracotomy will be excluded from the efficacy assessment.

The adhesion severity will be evaluated at the following five predefined sites: (i) anterior surface of the right ventricle, (ii) right lateral surface of the right atrium, (iii) diaphragmatic surface, (iv) left lateral surface of the left ventricle, and (v) surface of the ascending aorta. Adhesion severity will be evaluated using a four-grade scoring system where 0 = no adhesion, 1 = filmy and avascular adhesion, 2 = dense/vascular adhesion, and 3 = cohesive adhesion (Fig. 2) [11].

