### Study Endpoints

The primary outcome measure is the severity of adhesions at the five predefined sites (Fig. 2). This measure will be summarized in the following two ways: (1) total score of the severity of adhesions across all five sites, ranging from 0 (no adhesions at any of the five sites) to 15 (cohesive adhesions at all five sites); (2) total number of sites with dense/vascular or cohesive adhesions, ranging from 0 (no adhesions or filmy and avascular adhesions at any of the five sites) to 5 (dense/vascular or cohesive adhesions at all five sites). These two summary measures will serve as multiple primary endpoints. As adhesion formation generally begins immediately after surgery, and no new adhesion formation occurs after 1 week postoperatively, the severity of adhesions measured at 2 weeks or more after the primary thoracotomy will be used in the primary analysis of the two primary endpoints [15].

The secondary endpoints are: (1) total score of the severity of adhesions across all five sites at 1–12 weeks after the primary thoracotomy, (2) total number of sites with dense/vascular or cohesive adhesions at 1–12 weeks after the primary thoracotomy, (3) survival at the end of the observation period, (4) re-thoracotomy for hemostasis after primary thoracotomy, (5) transfusion volume during re-thoracotomy, and (6) absence of mediastinitis requiring surgical intervention.

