### Sample Size

The sample size was calculated based on the total adhesion severity score, assuming a mean difference in total score of 5.0 between the two groups and a standard deviation of 3.5, referring to published data [11]. Thus, 12 patients are required in each group, assuming a two-sided t-test with *α* = 0.05 with a power of 80%, and a simple Bonferroni correction to control the type I error rate due to the existence of two primary endpoints (a total alpha of 0.05 was equally allocated to each endpoint, i.e., *α* = 0.025). Based on the simulation, in most scenarios that were considered, a sample size of 12 in each group provided at least 80% power to detect a frequency difference in the total number of sites with dense/vascular or cohesive adhesions across all five sites, using the two-sided Fisher’s exact test at α = 0.025. To allow for a drop-out rate of 30% for the primary analysis of the primary endpoints, 15 patients will be recruited per group, i.e., 30 patients in total.

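### The adhesion grades behind both primary endpoints come from the re-thoracotomy operator in an open-label trial, with no masked grader named, so assessor bias can enter both endpoints

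*Protocol article*

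**What the plan says.** Study Setting fixes the design: "The study is an investigator-initiated, multicenter, pivotal, two-arm, open-label, randomized trial". Group Allocation gives the position on blinding: "Owing to the nature of the intervention, the investigators cannot be blinded to the allocations". It then names the grader: "Assessments regarding adhesion severity will be conducted by the operator of the re-thoracotomy in the presence of the cardiothoracic surgeon who is not involved"; the sentence goes on to specify the primary thoracotomy. The next sentence adds: "Video footage of the surgical field will be collected during re-thoracotomy".

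Assessment of Adhesion describes the measurement: "Pericardial adhesion will be macroscopically evaluated during VAD explant surgery performed 2–12 weeks after the primary surgery". Each of five sites receives a grade from 0 to 3. Study Endpoints derives two quantities from those grades: the total (0 to 15) and the number of sites graded 2 or 3 (0 to 5). On these it says: "These two summary measures will serve as multiple primary endpoints".

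The article nowhere gives the attending surgeon a grading or adjudicating role, says that this surgeon is kept unaware of the arm, or says how the video will be used.

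**The concern.** The grade is a judgement by eye on a four-step scale. The person making it belongs to a team that the article says cannot be blinded. If that person leans, even slightly and without intent, the lean is repeated over five sites and appears as a treatment difference. Both primary endpoints use the same five grades, so they tend to move together. The Bonferroni–Holm procedure in Statistical Methods protects against testing two endpoints by chance; it does not protect against a shift common to both. A larger sample does not help either, because the shift stays while the standard error shrinks.

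The trial is called pivotal, and Background gives approval in Japan as the subsequent goal. Unmasked grading would be hard to defend once the results are known. Two elements of a remedy, a second surgeon in the room and a recording, are already in the plan, but neither has a stated part in the scoring.

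**Working it through.** **Step 1. Does the stated reason cover the grader?** The reason is the nature of the intervention. It plainly holds for the surgeon who sprays the gel at the first operation. For a grader at the second operation, Background says of the gel: "this hydrogel coating is sustained for 7 days before being hydrolyzed". The primary analysis uses gradings from 2 weeks onward, so by then the coating should have passed its stated duration. The reason therefore does not carry over by itself to a grader who was absent from the first operation.

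**Step 2. The plan's own figure.** Sample Size works from "assuming a mean difference in total score of 5.0 between the two groups and a standard deviation of 3.5", with a two-sided t-test, alpha 0.025 per endpoint and 80% power, and states 12 per group.

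- Normal approximation: n = 2 × (2.241 + 0.842)² × (3.5/5.0)² = 9.3, so 10 per group.
- Exact noncentral t: 11 per group gives 81.5% power; 12 per group gives 85.4%.

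The stated 12 is sufficient and close to the exact minimum, so the same SD, n and alpha are used below.

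**Step 3. Effect of an assumed lean on the total score.** The leans are assumptions; the document gives none. Suppose there is no true effect and each site in group A is graded lower by δ on average.

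- Shift on the total = 5δ
- Standard error = 3.5 × √(2/12) = 1.429
- Noncentrality = 5δ / 1.429, with 22 degrees of freedom
- Critical t at two-sided 0.025 = 2.405, so significance needs an observed difference of 2.405 × 1.429 = 3.44 points, or 0.69 grade per site

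| Lean per site δ | Shift on total | Noncentrality | Rejection rate, 12 per group | Rejection rate, 15 per group |
|---|---|---|---|---|
| 0 | 0 | 0 | 2.5% | 2.5% |
| 0.1 | 0.5 | 0.35 | 3.3% | 3.5% |
| 0.2 | 1.0 | 0.70 | 5.9% | 6.9% |
| 0.3 | 1.5 | 1.05 | 10.6% | 13.2% |
| 0.5 | 2.5 | 1.75 | 27.7% | 35.5% |

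Counting only false wins for BAX602, the rate with 12 per group is 1.25% with no lean and 5.7% with a lean of 0.2.

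**Step 4. Both endpoints together.** A simulation used assumed grade probabilities of 0.15, 0.25, 0.35 and 0.25 for grades 0 to 3 and a latent between-site correlation of 0.5. The total score then has an SD of about 3.7, near the planned 3.5. Group A sites graded above 0 were lowered by one grade with probability q. Welch's test was applied to both endpoints at 0.025, with 12 per group and 20,000 trials per setting.

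| q | Shift, total score | Shift, number of sites | Total score significant | Site count significant | At least one significant |
|---|---|---|---|---|---|
| 0 | 0.0 | 0.0 | 2.5% | 2.6% | 3.4% |
| 0.2 | 0.8 | 0.35 | 4.8% | 4.5% | 6.0% |
| 0.4 | 1.7 | 0.70 | 12.2% | 10.8% | 14.2% |

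Both endpoints shift, and the chance of at least one false finding rises despite the split of alpha. Sample Size names Fisher's exact test for the site count, so that column is indicative only.

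**The case against.** The article shows an opening for bias, not bias. That the re-thoracotomy operator knows the arm is inferred from the open-label design and the general statement about investigators; it is not said of this operator, nor is it said whether the same person did the first operation. This stands, and it is why the point is that bias can enter.

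A reader might infer that nothing in the field could reveal the arm after 7 days. The article does not say that. It gives the duration of the coating, not the absence of visible residue or tissue change at day 14. The planned difference of 5 points on a 15-point scale could itself hint at the arm. Masking may therefore be imperfect.

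The sizes rest on assumed leans that are equal on average over five sites. A lean of 0.1 to 0.2 grade has a modest effect; the 27.7% needs half a grade at every site, which is not small. The site count moves only when a grade crosses from 2 to 1. These limits stand.

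A reader might also call this the main threat to the result. No comparison supports that: the plan also allows 30% drop-out from the primary analysis and excludes explants before day 14 from efficacy, and that selection could matter as much.

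Finally, the attending surgeon and the video may be meant as safeguards, and a condensed article may leave the use of the video to the full protocol. That is fair for the video. The grader, however, is named in the article, and the presence of a second surgeon without an independent masked score does not remove a lean.

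**Conclusion.** The point holds as an avoidable exposure. A stated rule gives the grading behind both primary endpoints to the operator in an open-label trial, and the reason offered does not explain why a grader weeks later must be unmasked. The documents do not show that bias is present or how large it would be. Under the planning assumptions and no true effect, the rejection rate for the total score goes from 2.5% to between 3.3% and 27.7% for assumed leans of 0.1 to 0.5 grade per site; the lower part of that range is the more cautious reading. Masked grading leaves the planned numbers unchanged. If it removed the lean entirely, the rate for the total score would return to 2.5%. The case for change rests on the low cost of the remedy and the regulatory aim, not on any demonstrated distortion.

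**What to change.** Amend Group Allocation so that:

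- the surgeon who already attends the re-thoracotomy, and who took no part in the primary thoracotomy, is kept unaware of the allocation;
- this surgeon records the five site grades independently, before any discussion with the operator, and these grades form the primary score for both endpoints;
- the operator also records grades, which are analysed as a sensitivity analysis, with agreement between the two sets reported;
- the case report form asks whether the assessor knew the arm at the time of grading.

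The cost is protocol and case report form wording, plus the effort at each site of keeping the allocation from one person. No extra staff, procedures or patients are needed.

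There are three downsides. Masking may fail at small sites, which is why knowledge of the arm should be recorded. An observer may separate some grades less well than the operator who dissects; the agreement report will show how often they differ. Trial Status says that enrolment began in January 2020, so any patient scored before the change will have only the operator's grades. Those patients should be flagged in the analysis, with results shown with and without them. The article does not say whether the video can separate all four grades at all five sites, so it should not be relied on to fill that gap without a check.

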### Trial Device

BAX602 is not approved in Japan, although it has been approved and is being sold in several Western countries. BAX602 is composed of three parts: the syringe pre-filled with the spray solution, the product-specific gas-driven spray device, and the spray kit that includes the tube and spray head. The spray solution is composed of two synthetic PEGs (a dilute hydrogen chloride solution and a sodium phosphate/sodium carbonate solution) provided in kits of 8 mL.

### Treatment Methods

The treatment flowchart is shown in Fig. 1. Surgery will be performed by the median sternotomy approach in all patients in both groups, with the inflow of the VAD being the LV apex and the outflow being the ascending aorta with or without the main pulmonary artery. In group A, prior to sternal closure, the spray device and the spray kit will be used to spray 8 mL of BAX602 in a thin homogeneous layer on the mediastinum, covering the visible surface of the heart and great vessels. In group B, no agent will be applied prior to sternal closure.

### Follow-Up

All patients will be followed up to detect any adverse events for 4 weeks after the primary surgery or until re-thoracotomy, whichever is longer. Follow-up will end at 12 weeks after the primary surgery of the last patient (last patient-out). The study schedule is shown in Table 2. The second surgery, in which the degree of pericardial adhesion will be assessed, will be performed via the re-median sternotomy approach.

**Table 2 Tab2:** Schedule of evaluation during the study

	Screening	Primary thoracotomy		4 weeks after the thoracotomy	Re-thoracotomy
		before	after		
Inclusion/exclusion criteria	X				
Signed consent form	X				
Medical/treatment history	X				
Vital signs		X			
Cardiac echography	X				X
Chest Xray	X				X
Laboratory tests	X			X	X
Surgical procedure of the primary thoracotomy			X	X	
Surgical procedure of the re-thoracotomy					X
Medication			X	X	X
Adverse events					
Survival				X	X

### Sample Size

The sample size was calculated based on the total adhesion severity score, assuming a mean difference in total score of 5.0 between the two groups and a standard deviation of 3.5, referring to published data [11]. Thus, 12 patients are required in each group, assuming a two-sided t-test with *α* = 0.05 with a power of 80%, and a simple Bonferroni correction to control the type I error rate due to the existence of two primary endpoints (a total alpha of 0.05 was equally allocated to each endpoint, i.e., *α* = 0.025). Based on the simulation, in most scenarios that were considered, a sample size of 12 in each group provided at least 80% power to detect a frequency difference in the total number of sites with dense/vascular or cohesive adhesions across all five sites, using the two-sided Fisher’s exact test at α = 0.025. To allow for a drop-out rate of 30% for the primary analysis of the primary endpoints, 15 patients will be recruited per group, i.e., 30 patients in total.

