### Statistical Methods

Analysis will be based on the intention-to-treat principle. Continuous data will be presented as mean ± standard deviation or median and range. Categorical data will be presented as frequencies with proportions (%). Group A will be compared with group B for all primary and secondary analyses. For intergroup comparisons, Fisher’ exact test will be used for categorical variables, while Welch’s t-test or Wilcoxon’s rank sum test will be used for continuous variables. In addition, the differences between means or proportions for continuous or categorical variables will be calculated with corresponding 95% confidence intervals, where appropriate.

The two primary endpoints will be analyzed by the Bonferroni–Holm procedure, with equal *α* allocation to control the type I error rate; both endpoints will first be tested at α = 0.025. If one of the endpoints significantly differs between groups but the other does not, the other endpoint will be tested again at the α = 0.05 level.

For the secondary endpoints, categorical variables will be assessed with the chi-square test or Fisher’s exact test, while continuous variables will be assessed with the t-test or Wilcoxon’s rank-sum test, as appropriate. For time-to-event variables, the event-free survival curve will be estimated using the Kaplan–Meier method and will be compared between the two groups using the log-rank test. The hazard ratio with its 95% confidence interval will be calculated using a proportional hazards model.

The analyses will be conducted using the most recent version of SAS (Cary, NC, USA). All tests will be two-sided. The statistical analysis plan, which includes a more technical and detailed elaboration of the principal features stated in the present protocol, will be prepared separately and finalized before the database is locked.

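### The second primary endpoint is an ordered 0–5 count per patient, but the only test named for it is Fisher's exact test with no stated unit: inefficient if applied to patients, invalid if sites are pooled

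*Protocol article*

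**What the plan says.** All references are to the protocol article; the separate analysis plan is not available.

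- **Study Endpoints** defines the second of two primary endpoints as the "total number of sites with dense/vascular or cohesive adhesions, ranging from 0" up to 5. It is a single ordered number for each patient.
- **Sample Size** derives 12 patients per group from the other primary endpoint, the total score, "assuming a mean difference in total score of 5.0 between the two groups and a standard deviation of 3.5". For the count, it speaks of detecting a difference in frequency and describes the quantity and its test as "total number of sites with dense/vascular or cohesive adhesions across all five sites, using the two-sided Fisher’s exact test". The significance level for this is 0.025, and the power claimed with 12 patients per group is 80% or more. That claim carries a qualifier: "Based on the simulation, in most scenarios that were considered". The section gives no site-level rates, no within-patient correlation and no layout of the table to which Fisher's test is applied.
- **Statistical Methods** says that Fisher's "exact test will be used for categorical variables", and that Welch's t-test or Wilcoxon's rank-sum test serves for continuous ones. It does not assign the count to either class. Both primary endpoints enter a Bonferroni–Holm procedure at 0.025 each. If only one is significant, the other is retested at 0.05.

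**The concern.** Fisher's exact test compares unordered categories. It can be applied to this endpoint in two ways, and neither suits a 0–5 count.

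- **By patient (2×6 table).** The categories 0, 1, …, 5 are treated as mere labels, so a consistent shift towards fewer sites gets no credit for its direction.
- **By site (2×2 table, 12 × 5 = 60 sites against 60).** The five sites of one patient are treated as independent, although patients are randomized.

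Under Holm, either primary endpoint can be declared significant on its own. The first way costs power on a primary endpoint. The second would put the familywise error rate at risk in a trial that the protocol calls pivotal and that is meant to support approval in Japan.

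**Working it through.** **1. The plan's own figure for the total score.** Inputs from Sample Size: difference 5.0, SD 3.5, two-sided α = 0.025, power 80%. The normal approximation is n = 2(z₀.₉₈₇₅ + z₀.₈₀)² × (3.5/5.0)² = 2 × (2.241 + 0.842)² × 0.49 ≈ 9.3, so 10 per group. The noncentral t gives 81.5% power at 11 and 85.4% at 12 per group. The planned 12 is adequate for this endpoint.

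**2. Are sites within a patient correlated?** A score limited to 0–3 has variance at most 1.5² = 2.25. Five independent sites therefore give a total SD of at most √(5 × 2.25) = √11.25 = 3.35, which is below the planned 3.5. Average within-patient correlation must be positive. For its size, solve 3.5² = 5s²(1 + 4ρ), where s is the assumed SD of one site's score:

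| s | ρ = (12.25/(5s²) − 1)/4 |
|---|---|
| 1.0 | 0.36 |
| 1.1 | 0.26 |
| 1.2 | 0.18 |
| 1.5 (maximum) | 0.02 |

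The sign follows from the plan's SD. The size depends on s, which the protocol does not give.

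**3. Power and type I error for the count, calibrated to 5.0/3.5.** The 80% cannot be reproduced directly because its scenarios are not reported. Assumed model: each 0–3 site score is a cut latent normal variable with a shared patient effect. Control means range from 8 to 12.5, the BAX602 mean is 5.0 lower, and the correlation is chosen so that the total SD is within 0.2 of 3.5. There are 23 settings, 12 per group, α = 0.025, with 1,000 trials each for power and 2,000 under the null.

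| Test | Power | Type I error |
|---|---|---|
| Fisher, 2×6 by patient | 38–68% | 1.5–2.8% |
| Wilcoxon on the count | 66–77% | 1.6–2.5% |
| Welch t on the count | 65–79% | 1.4–2.9% |
| Fisher, sites pooled 60 vs 60 | 87–96% | 4.8–24% |

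The Monte Carlo standard error is at most √(0.25/1000) = 1.6 points for power and √(0.025 × 0.975/2000) = 0.35 points for a true type I error of 2.5%. Three further settings of the same kind (3,000 trials each) gave 43–52% for 2×6 Fisher, 74–76% for exact Wilcoxon, and 91–95% apparent power with 9–13% type I error for pooled Fisher.

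**4. When does 2×6 Fisher reach 80%?** Assumed beta-binomial counts, 12 per group, α = 0.025:

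| Site rates | ICC 0 | ICC 0.2 | ICC 0.4 | ICC 0.6 |
|---|---|---|---|---|
| 0.7 vs 0.3 | 79% | 49% | 44% | 44% |
| 0.8 vs 0.4 | 82% | 56% | 47% | 47% |
| 0.8 vs 0.3 | 97% | 81% | 71% | 67% |
| 0.8 vs 0.2 | 99.8% | 95% | 90% | 88% |

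In the calibrated settings of step 3 the site rates differed by about 0.33 to 0.50. So 80% needs either a larger difference or weaker correlation. Under the same beta-binomial model the pooled test's type I error is 1.2–1.7% at ICC 0, 7% at 0.2, 13% at 0.4 and 19–20% at 0.6.

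**The case against.** The strongest reply has four parts.

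- **Fisher is not fixed as the final analysis.** It appears for this endpoint in a powering statement. The Statistical Methods section would allow Wilcoxon if the count is treated as continuous, and it leaves detail to the analysis plan. This stands. The firm defect is that the three sections do not settle on one suitable test and unit.
- **The 80% is not refuted.** It is claimed for most of the scenarios considered, which are not reported, and 5.0/3.5 is stated for the total score, not for the count. This stands too. A reader might infer that the power claim is false, but step 4 shows effects at which it is true.
- **Pooling is conjecture.** A reader might infer that the plan tests 60 sites against 60 and so loses control of α. The protocol does not say so: the endpoint is defined per patient and the sample size counts patients. The wording about a frequency difference across five sites leaves that analysis open, no more. The 2×6 analysis holds α, so it is inefficient but not invalid.
- **Power at 0.025 ignores Holm's second step.** Correct. In two settings with a difference of about 5.2 and SD 3.4–3.5, Wilcoxon power rises from 77–79% to 84–85% once the retest at 0.05 is counted, and 2×6 Fisher from 50–59% to 60–69%. Power to succeed on at least one endpoint was 85–88% even with 2×6 Fisher.

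These points narrow the claim. They do not make Fisher's test a good choice for an ordered count, and they do not supply the missing unit of analysis.

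**Conclusion.** The concern holds in a conditional form. The only test the protocol names for an ordered, per-patient primary endpoint either discards the ordering or, if sites were pooled, treats correlated sites as independent.

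At effects consistent with the total-score assumptions, 2×6 Fisher has about 38–68% power at 12 per group and α = 0.025, while Wilcoxon has about 66–77%. The stated 80% therefore requires larger effects or weaker within-patient correlation than those assumptions suggest. Even the better test does not reach 80% at the first Holm step. Pooling would raise the type I error to about 5–24% in the calibrated settings.

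The power and error ranges rest on an assumed latent-normal model. That sites are positively correlated rests only on the plan's SD of 3.5 against the 3.35 bound. This is an inexpensive improvement to make before analysis. It does not show that the trial is invalid or that its main power calculation is wrong.

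**What to change.** 1. State that the patient is the unit of analysis for the second primary endpoint and that sites are not pooled across patients.
2. Test the 0–5 count with an exact or permutation Wilcoxon rank-sum test, two-sided, within the existing Bonferroni–Holm procedure.
3. Report the difference in mean number of affected sites per patient with a patient-level confidence interval.
4. Replace the power sentence with the power of that test, giving the site rates, the within-patient correlation and the α used. Under the latent-normal model calibrated to 5.0/3.5, this is about 66–77% at the first-step α of 0.025, and higher when the second step at 0.05 is counted.

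The cost is wording and a re-run simulation, with no new data. The protocol says that the analysis plan is finalized before database lock, so the test and unit can be fixed there. The price is a possibly less favourable stated power for this endpoint.

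### Recruiting 15 per group allows for 20% drop-out, not the stated 30%; at 30% loss about 10-11 per group remain, and total-score power is at or slightly below 80%

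*Protocol article*

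**What the plan says.** The Sample Size section of the protocol article bases the calculation on the total adhesion score, "assuming a mean difference in total score of 5.0 between the two groups and a standard deviation of 3.5". It uses a two-sided t-test with 80% power. Because there are two primary endpoints, "a total alpha of 0.05 was equally allocated to each endpoint", which gives 0.025 each. The result is: "Thus, 12 patients are required in each group".

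For the second primary endpoint, the number of sites with dense/vascular or cohesive adhesions, the section relies on a simulation: "in most scenarios that were considered, a sample size of 12 in each group provided at least 80% power". The scenarios are not given.

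The inflation step follows: "To allow for a drop-out rate of 30% for the primary analysis of the primary endpoints, 15 patients will be recruited per group", or 30 patients in all.

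Two other places bear on this. Under Assessment of Adhesion, patients re-operated on days 1-13 do not count for efficacy, so some loss from the primary analysis is built into the design. Under Statistical Methods, the two primary endpoints are tested by Bonferroni-Holm: each at 0.025 first and, if only one succeeds, the other again at 0.05.

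**The concern.** The required number, the loss rate and the recruitment figure stand in the same section and cannot all hold. The stated loss is specifically loss from the primary analysis, so it cannot be read as a general drop-out rate with a smaller loss for the primary endpoints. This is also not detail left to the analysis plan: the article gives the inputs and the result, and the result does not follow.

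At stake is whether the planned case, 30% loss, still delivers the stated power for the two primary endpoints of a trial that is called pivotal and is meant to support approval in Japan.

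**Working it through.** **Inputs.** From Sample Size: difference 5.0, SD 3.5, alpha 0.025 two-sided, power 80%, 12 evaluable per group, 30% loss, 15 recruited per group. From Group Allocation: 1:1 allocation.

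**Step 1: the plan's base figure.** Standardised difference d = 5.0/3.5 = 1.4286. Power comes from the noncentral t distribution with n1 + n2 - 2 degrees of freedom and noncentrality 5.0 / (3.5 × √(1/n1 + 1/n2)). The smallest n per group that reaches 80% is 11 by the exact t-test (10 by the normal approximation). The stated 12 is therefore sound and carries a margin: at 12 + 12 the noncentrality is 3.499, the critical value 2.406 and the power 85.4%.

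**Step 2: the inflation.**
- To keep 12 after 30% loss: 12 / (1 - 0.30) = 17.14, so 18 per group (36 in total).
- By the common shortcut: 12 × 1.30 = 15.6, so 16 per group. It gives 15 only if rounded down.
- Loss that 15 per group really covers: 1 - 12/15 = 0.20.
- Evaluable after 30% loss: 15 × 0.70 = 10.5 per group, or 30 × 0.70 = 21 in total.

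The stated 15 does not reproduce at 30%. It reproduces exactly at 20%.

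**Step 3: power for the total score at the numbers that remain.**

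| Evaluable | alpha 0.025 (sizing basis) | alpha 0.05 (second Holm step) |
|---|---|---|
| 12 + 12 | 85.4% | 91.7% |
| 11 + 11 | 81.5% | 89.0% |
| 10 + 11 | 79.1% | 87.3% |
| 10 + 10 | 76.6% | 85.5% |
| Average over random 30% loss from 15 per arm | 77.7% | 86.1% |

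The average weights the power at each pair of evaluable numbers by independent binomial(15, 0.70) probabilities. Welch's version of the test, simulated with 100,000 runs, gives 78.3% at 11 + 10 and 76.2% at 10 + 10 at alpha 0.025, within one point of the table.

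**Step 4: the site-count endpoint.** Power at 10 or 11 per group cannot be derived, because the simulation scenarios are not stated. Purely as an assumption, take independent sites pooled in Fisher's exact test at alpha 0.025:

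| Assumed site rates | 10 per group | 11 per group | 12 per group |
|---|---|---|---|
| 20% vs 50% | 78.2% | 82.6% | 86.5% |
| 30% vs 60% | 71.8% | 79.1% | 81.4% |
| 20% vs 60% | 96.4% | 97.8% | 98.7% |

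The answer depends on the scenario. A scenario that only just meets 80% at 12 per group does not meet it at 10.

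**The case against.** The division cannot be defended, but its consequence can be argued down, and much of that argument stands.

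- **12 is not the 80% threshold.** The exact t-test needs 11 per group, and 12 gives 85.4%, so the margin absorbs most of the extra loss. At 21 evaluable patients the shortfall is about one point (79.1%), and about two points averaged over random loss (77.7%). This stands. It does not remove the shortfall entirely: 11 + 11 needs 22 evaluable patients, and 30% loss leaves 21.
- **The analysis is Holm, not simple Bonferroni.** If the site count is significant at 0.025, the total score may be tested at 0.05, where average power at 30% loss is 86.1%. Power for the total score under Holm thus lies between 77.7% and 86.1%, and the article does not allow a closer figure. This stands: the shortfall is shown on the sizing basis only.
- **A reader might infer that the trial is clearly underpowered at its planned loss.** The figures do not support that for the endpoint that sized the trial. One could also point to the roughly 9% chance that both arms keep 12 patients at 30% loss. The same measure gives only 42% at 20% loss, where the inflation is correct, so it says little about power.

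None of this covers the site-count endpoint, for which the article claims power at 12 per group only, and not in every scenario.

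**Conclusion.** The sentence is wrong as written and should be fixed. 15 per group covers 20% loss, and the stated 30% would need 18. This part is arithmetic on the article's own figures and rests on no assumption.

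The effect on power is modest. At 30% loss the total score has about 77-81% power at alpha 0.025, against about 85% at 12 per group, so it is at or slightly below the stated 80%. That rests on the plan's difference and SD, normally distributed scores, and a t-test; the averaged figure also assumes independent random loss at the same rate in both arms. No test, alpha allocation or estimate is affected.

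The less visible gap is the site-count endpoint, whose power at 10-11 per group has no support in the article. It may be adequate or not; the illustrative rates above show both.

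**What to change.** Correct the sentence without enrolling more patients. The preferred form keeps the 30% assumption:

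1. State that 15 per group leaves about 10-11 evaluable per group (21 of 30) after 30% loss.
2. State that this gives about 77-81% power for the total score at alpha 0.025.
3. Report the simulated power of the site-count endpoint at 10 and 11 per group, with the scenarios used.

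The alternative is to state the allowance as 20%, since 15 × 0.80 = 12. This is right only if the sponsor really expects 20% loss; the rate should not be lowered merely to match the enrolment figure.

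The cost is one or two sentences, a re-run of the existing simulation at two smaller sample sizes, and a slightly less favourable stated power.
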